#### Strategies to improve adherence to interventions {11c}

The date and quantity of medicine distribution and return will be recorded. Participants will be required to return both the finished medicine package and unused medicine. Furthermore, providing free health education consultations and daily care for participants will improve adherence to interventions.

#### Relevant concomitant care permitted or prohibited during the trial {11d}

Participants will be discouraged from receiving any other treatment or medication during the study period to prevent any effect on the results. During treatment, if there is substantial exudate or severe itching, the patient will be allowed to moisten the exudate area with the Pifukang solution (specification 50 mL/bottle, national medicine quasi-word Z19990045; Beijing Huayang Kuilong Pharmaceutical Co., Ltd.) 2–4 times a day. An eight-layer medical gauze will be dipped into the diluted lotion, which has been diluted six times with cooled boiled water at 4–10°, gently wrung out, and then applied to the affected skin. Loratadine tablets (Caretan, specification 10 mg × 6 tablets, national medicine quasi-word H10970410; Bayer Medicine (Shanghai) Co., Ltd.) will also be allowed to be taken orally once a day, 10 mg each time, if itching is difficult to resist. Details of the prescriptions and medications used will be recorded in the CRF. The proportion of participants using rescue drugs will be compared between the two groups. The use of other TCMs is prohibited.

#### Provisions for post-trial care {30}

If an adverse event occurs during the clinical trial, the committee of medical experts will determine whether it is related to the Longmu Tang granule. Xiyuan Hospital of China Academy of Chinese Medical Sciences will cover the cost of treatment and the corresponding economic compensation for the damage related to the trial.

### Outcomes {12}

#### Primary outcome

The primary outcome of the trial is the efficacy of the Longmu Tang granule in improving the clinical symptoms of patients with AD after 8 weeks of treatment. The main evaluation of the primary outcome will be the change in the SCORAD score [18] from baseline to the end of the 8-week treatment. SCORAD was proposed by the European Task Force on AD. SCORAD includes the area (A) and severity (B) of skin lesions and the subjective symptoms of pruritus and their effects on sleep (C). The *SCORAD* system is internationally recognised as the gold standard for AD scoring. The SCORAD score ranges from 0 (best) to 103 (worst), with a minimal clinically important difference (MCID) of 8.7 [19]. Higher scores indicate more severe symptoms. The SCORAD scores of the participants before and after treatment will be statistically analysed.

#### Secondary outcomes

The change in the Children's Dermatology Life Quality Index (CDLQI) score [20] (from baseline to week 8): the CDLQI is the most commonly used life index score of dermatological quality. This study will recruit children aged 6–12 years, so the CDLQI score will be used. The total CDLQI score ranges from 0 (best) to 30 (worst), with 6 as the MCID [21].The change in the number cancellation test (NCT) score (from baseline to week 8): the NCT is a traditional method used to evaluate attention function; the NCT score will be measured before and after the treatment, respectively, for 3 minutes each time, including the NCT net score and cancellation error rate, number of times of correct cancellation (the greater the better), number of times of incorrect cancellation, and number of times of omitted cancellation (the less the better), which will be compared before and after treatment. Raw score = the number of times of correct cancellation; net score = raw score – (the number of times of incorrect cancellation + 1/2 of the number of times of omitted cancellation); error rate = (the number of times of incorrect cancellation + 1/2 of the number of times of omitted cancellation) / raw score × 100%.Participants’ expectations of the Longmu Tang granule will be assessed at baseline using the following two questions: “Do you think the Longmu Tang granule will be effective for treating the illness?” and “Do you think the Longmu Tang granule will be effective for relieving the related symptoms of AD?” The response options will be ‘yes’, ‘no’, or ‘unclear’.Integral TCM syndrome score (from baseline to week 8 and 12; the scores and details are presented in Tables 2 and 3). A scale of 0–6 points is used to score patients with AD according to the severity of clinical symptoms.Significantly effective: inhibition or complete suppression of primary and secondary clinical symptoms and reduction of the syndrome score by ≥ 95%Effective: significant improvement in clinical symptoms and reduction in the syndrome score by 70–95%Ineffective: improvement in clinical symptoms and reduction in the syndrome score by 50–70%Invalid: reduction of treatment syndrome score by < 50%Long-term control: the evaluation of long-term control will be based on the change in the SCORAD score and change in the CDLQI score from baseline to the end of the 8-week follow-up after treatment.

**Table 2 Tab2:** Traditional Chinese medicine syndrome score

	None	Mild		Moderate		Severe	
Primary symptoms							
Itch	0	2		4		6	
Patterns of skin lesion	0	2		4		6	
Area of skin lesion	0	< 10%	10–29%	30–49%	50–69%	70–89%	90–100%
	0	1	2	3	4	5	6
Secondary symptoms							
Restlessness	0	1		2		3	
Dry mouth	0	1		2		3	
Sleeplessness	0	1		2		3	
Dry stool	0	1		2		3	
Scanty dark urine	0	1		2		3

**Table 3 Tab3:** Detailed description of symptoms according to Traditional Chinese medicine

	None	Mild	Moderate	Severe
Itch	No symptom	Occasional occurrence and no influence on study and life	Regular occurrence and have influence on study and life	Frequent occurrence and have serious influence on study and life
Patterns of skin lesion	No symptom	Erythema, papules, or blisters	Oozing	Skin thickening (lichenification)
Area of skin lesion	Calculated based on PASI score			
Restlessness	No symptom	Slight	Heavy	Heavy; irritable
Dry mouth	No symptom	Slight; no need to drink water	Severe; need to drink water occasionally	Intolerable; need to drink water frequently
Sleeplessness	No symptom	Slower falling asleep or occasional waking	Difficult to fall asleep and wake up easily	Hardly able to sleep
Dry stool	No symptom	Dry stool; once per day	Dry stool, 1 time in 2–3 days	Difficult stool, > 3 days each time
Scanty dark urine	No symptom	Urine volume is fine, slightly yellowish in colour	Small amount of urine, yellow colour, slightly hot	Scanty dark urine

*Abbreviation*: *PASI* Psoriasis Area Severity Index

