### Statistical methods

#### Statistical methods for primary and secondary outcomes {20a}

Data analysis will be completed using the Statistical Package of Social Sciences software (version 22.0; IBM Corp.), according to the per-protocol and intention-to-treat principles. Normally distributed continuous variables will be reported as mean ± standard deviation, and non-normally distributed continuous variables will be reported as median (interquartile range). The two-independent sample *t*-test, Wilcoxon test, or paired *t*-test will be used to analyse continuous variables, and the chi-square test and Fisher exact probability test will be used to analyse categorical variables. The two-sided test will be used uniformly in the hypothesis testing. A *P-*value < 0.05 will indicate that the difference is statistically significant, and a *P*-value < 0.01 will indicate that the difference is highly statistically significant.

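### The TCM syndrome response classes share their cut-points at 70% and 95%, the 50–70% class has a label that contradicts its description, and the general test rule ignores the order of the classes

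*Protocol article*

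**What the plan says.** All quotes are from the protocol article. The Secondary outcomes section names the outcome as "Integral TCM syndrome score (from baseline to week 8 and 12; the scores and details are presented in Tables 2 and 3") and then defines four classes by percentage reduction:

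- Significantly effective: "reduction of the syndrome score by ≥ 95" per cent.
- "Effective: significant improvement in clinical symptoms and reduction in the syndrome score by 70–95" per cent.
- "Ineffective: improvement in clinical symptoms and reduction in the syndrome score by 50–70" per cent.
- "Invalid: reduction of treatment syndrome score by < 50" per cent.

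The same section introduces the score with "A scale of 0–6 points is used to score patients with AD according to the severity of clinical symptoms". Table 2 gives three primary items scored up to 6 and five secondary items scored up to 3.

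The statistical methods section {20a} has one rule per type of variable. For categories, "the chi-square test and Fisher exact probability test will be used to analyse categorical variables". The rank test appears only in the rule for continuous data: "Wilcoxon test, or paired *t*-test will be used to analyse continuous variables". No test is tied by name to the syndrome classes, and no sentence says which classes are pooled into a response rate. The sample size section {14} uses the SCORAD change only.

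**The concern.** A classification used as an efficacy outcome should put each child in exactly one class, and the class names should say which side of success a child is on. Here neither is secure.

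At 70% nothing in the text settles the tie, and this is the boundary between the classes named Effective and Ineffective. The third class is described as improved, is called Ineffective, and sits above another class that already holds the children who improved least. A reader given an effectiveness rate could not tell whether the 50–70% children were counted. The Discussion cites an efficacy rate of 70% from the team's earlier study without defining it. The scale behind that figure is not stated, but it suggests that such a rate may be reported again. If the choice is still open when the data are unblinded, it can be made with the results in view.

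The four classes are also ordered. If they go to the tests listed for categorical variables, that order is discarded.

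**Working it through.** **1. The plan's own figure.** No power or sample size is stated for the syndrome classes, so there is no figure for this outcome to reproduce. The only sizing is for SCORAD: d = (15 − 6.35)/8.69 = 0.995. A two-sided t-test at 5% with 90% power needs 22.2, so 23 per group, as stated. Adding 20% loss gives 46/0.8 = 57.5, so 58, against the stated 60.

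**2. Overlap.** Limits as printed:

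| Class | Lower limit | Upper limit | Shared value |
|---|---|---|---|
| Significantly effective | 95%, closed | none | 95% |
| Effective | 70%, unmarked | 95%, unmarked | 95% and 70% |
| Ineffective | 50%, unmarked | 70%, unmarked | 70% |
| Invalid | none | 50%, open | none |

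At 95% the explicit ≥ sign points to the upper class. At 70% neither limit is marked. At 50% the strict < sign removes any conflict.

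**3. How often a tie can occur.** Assume the total is the plain sum of the Table 2 items. The maximum is 3 × 6 + 5 × 3 = 33. For an integer baseline b from 1 to 33:

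- 0.70 × b is an integer only at b = 10, 20 and 30 (falls of 7, 14 and 21).
- 0.95 × b is an integer only at b = 20 (a fall of 19).

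Leaving out worsening, each baseline b allows b + 1 possible falls. That makes 33 × 34/2 + 33 = 594 pairs, of which 4 are ties. This counts attainable pairs; it is not a probability.

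**4. What the third class does to a response rate.** The protocol gives no distribution for the syndrome score. For illustration, assume normal percentage reductions with means 65% and 45% and SD 25.

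| Threshold | Active | Control | Difference |
|---|---|---|---|
| 70% | 1 − Φ(0.2) = 42% | 1 − Φ(1.0) = 16% | 26 points |
| 50% | 1 − Φ(−0.6) = 73% | 1 − Φ(0.2) = 42% | 31 points |

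Counting the 50–70% class as response raises the reported rate by 31 points in one arm and 26 in the other. In this example the difference between arms moves by only about 4 points, so the larger effect is on how the rates read.

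**5. Cost of ignoring order.** Category rates are also assumed. Control shares, from Invalid up to Significantly effective, are 60/25/12/3% (set A) or 50/25/20/5% (set B), with a proportional-odds shift and 2,000 simulated trials per scenario. Thirty per arm is everyone randomised; 24 is 30 × 0.8. Power of the four-class chi-square test against the Wilcoxon rank-sum test, two-sided 5%:

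| Odds ratio | n per arm | Set A | Set B |
|---|---|---|---|
| 2 | 30 | 17.2% v 28.4% | 18.2% v 30.6% |
| 3 | 30 | 42.0% v 61.6% | 44.8% v 63.0% |
| 4 | 30 | 63.8% v 81.6% | 65.6% v 81.3% |
| 6 | 30 | 87.0% v 95.6% | 88.2% v 95.6% |
| 3 | 24 | 34.5% v 50.9% | 36.2% v 53.0% |
| 4 | 24 | 51.7% v 70.5% | 53.2% v 72.6% |

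The gap runs from 95.6 − 88.2 = 7.4 points to 61.6 − 42.0 = 19.6 points. Pooling the top two classes does not recover it: at odds ratio 3 and 30 per arm, the uncorrected 2×2 chi-square has 41.7% (A) and 51.4% (B). Part of the gap arises because the chi-square test is slightly conservative with sparse cells: with no effect it rejected in 3.5 to 4.4% of trials, against 4.2 to 5.4% for the rank test.

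**The case against.** The strongest reply is that little here affects a result. Ties touch 4 of 594 pairs, and the ≥ sign reasonably settles the one at 95%. The numerical bands still order the classes, so an odd label moves no child from one class to another. All of this stands and limits the size of the point. It does not remove the unsettled tie at 70% or the clash between the third label and its description, both of which are on the page.

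A reader might infer that the protocol assigns a chi-square test to this outcome. It does not. The link comes from a general rule, the outcome is first named as a score, and a score change could go to the t-test or Wilcoxon test. An analysis plan that is not shown may settle this. What can be said is that, for the classes as categories, the only tests the rule offers ignore order.

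A reader might also infer that a responder analysis is planned and is underpowered. No responder is defined and no power is claimed for this secondary outcome, so no stated figure is contradicted. The power losses rest on assumed rates and a shift in one direction.

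Finally, the 0–6 scale might be taken to contradict a total of 33. It can be read as the range of item scores, which Table 2 bears out. This is loose wording and no more.

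**Conclusion.** The point holds as a minor to moderate defect in the definition of a secondary outcome. Three things need no assumption: the shared limit at 70%, the literal overlap at 95%, and a label at odds with its own description. Any effectiveness rate drawn from these classes could be read at either of two thresholds, 70% or 50%. The rarity of ties assumes an integer total of 0–33. The statistical cost, about 7 to 20 percentage points of power if the ordered classes are compared by an unordered chi-square test, depends on the assumed category rates and a consistent shift. The sample size and the primary SCORAD analysis are unaffected.

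**What to change.** - Make the bands exclusive: ≥ 95%; ≥ 70% to < 95%; ≥ 50% to < 70%; < 50%.
- Reconcile the label of the third class with its description, and state before unblinding which classes, if any, are pooled as response.
- Compare the ordered classes with a Wilcoxon rank-sum test or a proportional-odds model instead of an unordered chi-square test. Alternatively, lead with the baseline-adjusted change in the total score and report the classes descriptively.
- Optionally, say that 0–6 is an item range and that the Table 2 items sum to a maximum of 33.

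The cost is wording in the protocol and analysis plan. The scores are already to be collected, so no further visits, measurements or participants are needed.

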#### Exploratory outcomes

Serum inflammatory cytokines, such as serum immunoglobulin E, tumour necrosis factor-α, interleukin-1, and interleukin-6, will be detected using an enzyme-linked immunosorbent assay (ELISA) at baseline and week 8. ELISA kits have been purchased from Sigma-Aldrich.

#### Safety measures

Safety measures include laboratory indices (routine blood and urine test results, and kidney and liver function test results) and adverse events. All adverse events will be tracked for 16 weeks after randomisation.

#### Safety assessment

Full blood count and urine, kidney, and liver function tests will be performed before and after treatment. All details of severe adverse events (SAEs) and adverse events (AEs) will be recorded in the CRF. Any serious adverse events will be reported to the Ethics Approval Committee of Xiyuan Hospital of China Academy of Chinese Medical Sciences within 24 h. Safety will be monitored at every visit for up to 8 weeks after the end of the intervention.

#### Participant timeline {13}

The visit schedule for all assessments (baseline, primary outcome, secondary outcomes, exploration outcomes, and security indicators) is shown in Fig. 1. At each assessment timepoint, the same investigator will evaluate the participants. During the treatment period (i.e. from baseline to week 8), all combined therapeutic medicines will be recorded, including their name, dose, and course. Participants’ expectations of the Longmu Tang granule will be assessed at baseline. The primary outcome and CDLQI score will be evaluated at baseline and at the first, second, fourth, sixth, and last visits. Exploratory outcomes, NCT scores, and safety indicators will only be evaluated at baseline and at the last visit. Table 4 summarises the schedule of screening, enrolment, intervention, assessments, and data collection.

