#### Drop out criteria

Patients who voluntarily withdraw from the trial because of poor efficacy, adverse reactions, etc.Patients who are lost to follow-upPatients who use prohibited drugs in the protocol

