#### Sample size {14}

The sample size was calculated based on the primary outcomes, which were the change in the SCORAD score from baseline to the end of week 8. In our pilot trial [17], with 20 patients in the Longmu Tang group and 20 patients in the control group, the mean (± standard deviation) reductions in the SCORAD score after 8-week treatment were 20.76 ± 8.05 and 6.35 ± 8.69 in the Longmu Tang and control groups, respectively. In a previous study [22], the mean reduction in the SCORAD score in the Longmu Tang group was 15, with 31 patients in the Longmu Tang group and 31 patients in the control group. In another previous study [23], the mean reduction in the SCORAD score in the Longmu Tang group was 12.86, with 62 patients in the Longmu Tang group and 60 patients in the control group. Considering the three trials and number of patients in each of the three trials, we estimated the mean (± standard deviation) reduction in the SCORAD score after 8-week treatment in the experimental and control groups to be 15 ± 8.69 and 6.35 ± 8.69, respectively. Assuming an alpha risk of 5% and beta risk of 10% using the GPOWER software (version 3.1.9.7), a sample size of 46 (23 participants in each group) was calculated. Considering a 20% loss to follow-up, this trial will require 60 participants (30 participants in each group).

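### SCORAD and CDLQI are scored at intermediate visits, but the stated outcomes and tests use only two-point changes, and the two missing-data rules that could bring the other scores in do not agree

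*Protocol article*

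**What the plan says.** All references are to the protocol article.

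- **Participant timeline {13}:** "The primary outcome and CDLQI score will be evaluated at baseline and at the first, second, fourth, sixth, and last visits". It does not say whether these ordinals are weeks or visit numbers, and the schedule in Table 4 is not shown.
- **Primary outcome:** "the change in the SCORAD score [18] from baseline to the end of the 8-week treatment".
- **Secondary outcomes:** "The change in the Children's Dermatology Life Quality Index (CDLQI) score [20] (from baseline to week 8"; and, for long-term control, "change in the SCORAD score and change in the CDLQI score from baseline to the end of the 8-week follow-up after treatment".
- **Statistical methods {20a}:** "The two-independent sample *t*-test, Wilcoxon test, or paired *t*-test will be used to analyse continuous variables". Analyses follow both intention-to-treat and per-protocol principles.
- **Drop out criteria:** the first entry is "Patients who voluntarily withdraw from the trial because of poor efficacy, adverse reactions, etc".
- **Sample size {14}:** "Considering a 20% loss to follow-up, this trial will require 60 participants".
- **Discontinuation {11b}:** the final values recorded for participants who stop are to enter the analyses.
- **Non-adherence and missing data {20c}:** children with drug compliance under 80%, or who stop medication and testing, stay in the intention-to-treat analysis and leave the per-protocol analysis. Missing data are to be multiply imputed. No imputation variables are given.

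**The concern.** Every SCORAD and CDLQI outcome is a difference between two time points, and each listed test takes one value per child or one before-after pair. The scores in between have no place in the stated comparison unless a missing-data rule gives them one.

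Those scores matter because of who is expected to leave. In a placebo-controlled trial that foresees withdrawal for poor efficacy, non-improvers may leave more often on placebo. The control children still present at week 8 then look better than the whole control arm, and the difference shrinks. The intermediate scores of the leavers record the poor response, so an analysis that conditions on them can correct the shrinkage when dropout depends on observed scores. Whether this trial's analysis would do so depends on which of two conflicting rules is followed and on what the imputation model contains.

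**Working it through.** **1. The plan's own figure.** From Sample size {14}: reductions of 15 and 6.35, SD 8.69 in both arms, alpha 5%, beta 10%. Tests are two-sided under {20a}.

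- Difference: 15 − 6.35 = 8.65. Standardised: 8.65 / 8.69 = 0.995.
- A two-sided two-sample t-test at 90% power needs 22.2 per arm, so 23 per arm and 46 in total. This matches the protocol. Power at 23 per arm is 0.910.
- Allowing for 20% loss: 46 / 0.8 = 57.5, so 58. The stated 60 covers this.

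The sample size is not in question.

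**2. How many intermediate visits.** If the last visit is week 8, the other four are intermediate, but the end-of-follow-up score needed for long-term control is not listed. If the last visit is the end of follow-up, one of the four must be week 8, leaving three. The argument is the same either way.

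**3. Effect of leaving the intermediate scores out.** Simulations used 30 per arm and the protocol's means and SD (true difference 8.65). Assumptions not in the documents: scores at weeks 1, 2, 4, 6 and 8; linear mean improvement; the within-child correlation; and dropout driven by poor observed improvement. The all-visits results come from sequential regression on earlier visits, which approximates a repeated-measures model.

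| Assumptions | Week-8 completers: estimate, power | Last value forward: estimate, power | All visits: estimate, power |
|---|---|---|---|
| Mild: correlation 0.5–0.85; loss 15–17% active, 23–25% placebo | 7.9–8.4; 0.89–0.91 | 7.9–8.4; 0.77–0.84 | 8.5–8.7; power not computed |
| Stronger: two-week correlation 0.9; loss 14–21% active, 30–40% placebo across the stronger runs | 7.21; power not quoted | 8.4–9.0; 0.87–0.91 across the stronger runs | 8.66; 0.94 |
| Stronger: two-week correlation 0.7; loss range as above | 7.61; power not quoted | range as above | 8.74; 0.92 |
| Steep: two-week correlation 0.9; non-improvers at week 4 or 6 leave with probability 0.6; loss 9% active, 26% placebo | 6.87; 0.86 | not run | 8.66; 0.96 |

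Bias is the estimate minus 8.65:

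- Mild: 8.35 − 8.65 = −0.30 to 7.87 − 8.65 = −0.78.
- Stronger: 7.61 − 8.65 = −1.04 and 7.21 − 8.65 = −1.44; over correlations 0.6–0.9 the range was −1.0 to −1.7.
- Steep: 6.87 − 8.65 = −1.78.
- One heavier variant of the steep case (14% and 36% lost) went slightly further: 6.64 − 8.65 = −2.01, power 0.81.

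**4. Does imputation cure it?** Only if the intermediate scores are in the model. In the stronger setting, imputing from arm and baseline alone gave 7.21 and 7.61, identical to the completers, with power 0.88 and 0.85. Adding the intermediate visits gave the 8.66 and 8.74 in the table. A further run imputing from arm alone gave about 7.2 to 8.0 with power 0.85–0.89; there, last value forward was roughly unbiased with power 0.89–0.92, and all visits gave about 8.7 with power 0.91–0.95.

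**5. No true effect.** With equal loss of about 20% per arm, type I error was 0.049 for completers and 0.042 for last value forward.

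**The case against.** A reader might infer that the week-8 comparison throws the intermediate scores away and that nothing in the protocol uses them. The documents do not support that. Section {11b} puts the final recorded values of children who stop into the analyses, and for a child who leaves mid-treatment that is an intermediate score. Section {20c} promises multiple imputation, which may use those scores. A completer t-test is therefore not the planned intention-to-treat analysis, and its bias cannot be presented as the bias of the primary result. It bears on the per-protocol analysis, and on the intention-to-treat analysis only if the imputation model omits the intermediate scores.

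It can also be said that imputation variables belong in an analysis plan that is not shown, and that a mixed model rather than an imputed week-8 t-test is partly preference. Both have weight: a missing variable list is not in itself a fault, and well-informed imputation followed by a t-test does about as well. Two things still stand. The article does fix its tests, and they suit a two-visit design rather than the one it schedules. And {11b} and {20c} give different rules within the same document.

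On size, the protocol states only 20% loss, with no split by arm. Under the mild assumptions the completer test keeps about the planned 0.90 power, and using all visits gives no gain in precision (SD of the estimate about 2.4 to 2.5 either way). The gain there is in bias alone.

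**Conclusion.** The point holds in limited form. No stated SCORAD or CDLQI outcome or test uses the intermediate scores, and their only route in is through two missing-data rules that disagree. If dropout for poor efficacy is commoner on placebo, a completer analysis or imputation without those scores understates the difference by roughly 0.3 to 1.8 points on a planned 8.65, with power about 0.85–0.91. Carrying the last value forward shows less bias in most runs but has lower power than using all visits (about 0.77–0.92 across settings). Using all visits is close to unbiased, with power 0.91–0.96 where it was computed.

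The range reflects assumed correlation and dropout, and the upper end needs strong, unequal loss. The bias runs toward no effect, so the point gives no ground for fearing a false positive. It is worth correcting because the data are already scheduled, but it does not undermine the design.

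**What to change.** - **In {20a}:** analyse SCORAD with a repeated-measures mixed model over all post-baseline treatment visits, with arm, visit, arm-by-visit interaction and baseline SCORAD. Keep the week-8 arm contrast as the single primary test. Treat CDLQI likewise as a secondary outcome.
- **In {11b} and {20c}:** reconcile the two passages into one missing-data rule. Where imputation is kept, state that the intermediate scores are in its model.
- **In {13}:** say which week each listed visit falls in, so that the visits in the model are fixed.

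The cost is wording and slightly more analysis work. No new data are needed, and the planned software can fit the model. The model relies on data being missing at random given the observed scores; dropout that depends on unrecorded worsening would not be corrected.
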